## Abstract

**Background:**

Pressure dressings have been used after open hemorrhoidectomy to protect surgical wounds and manage postoperative bleeding for many years. However, pressure dressings may increase the incidence of postoperative complications, such as urinary retention, medical adhesive-related skin injury, and pain. A previous controlled trial included 67 patients who underwent Milligan-Morgan hemorrhoidectomy. The data indicated that the use of a nonpressure dressing after hemorrhoidectomy reduces the incidence of urinary retention and catheterization. However, the incidence of severe postoperative bleeding and other postoperative complications was not assessed. There is no consensus on whether it is necessary and beneficial to use a nonpressure dressing after hemorrhoidectomy. The results of this randomized clinical study will help answer this question.

**Methods:**

In this study, we plan to include 186 patients who have undergone modified Milligan-Morgan hemorrhoidectomy, which only sutured external hemorrhoids to reduce the risk of bleeding. The purpose is to determine whether the use of nonpressure dressings after open hemorrhoidectomy is inferior to the use of pressure dressings in terms of severe postoperative bleeding and postoperative complications. The primary endpoints of the trial are the incidence of urinary retention within 24 h after surgery and the incidence of severe postoperative bleeding 1 h after dressing removal, which requires revision surgery within 24 h after the surgery. The secondary endpoints of the study are the pain score, anal distension score, postoperative use of analgesics, and incidence of medical adhesive-related skin injury, all of which will be assessed before removing the dressings. The length of hospitalization in days and hospitalization expenses will be recorded. Safety will be assessed with consideration of all adverse and severe adverse events related to the study treatment.

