## Introduction

### Background and rationale {6a}

As people’s personal and work lifestyles change, the incidence of mixed hemorrhoids in China is increasing annually [1]. According to an epidemiological study, in 2016, the incidence of anorectal diseases among urban residents in China was 51.14%, and the incidence of mixed hemorrhoids was the highest among these diseases, accounting for 50.28% of all anorectal diseases [2]. In the USA, the incidence is approximately 4%, with the prevalence being highest between 45 and 65 years of age [3]. It is estimated that about 50% of Germans have symptomatic hemorrhoids, and some authors believe that up to 70% of people are affected by hemorrhoids [4]. Mixed hemorrhoids can occur at any age, and the symptoms include itching, pain, bleeding, swelling, prolapse of an anal tumor, foreign body sensation, etc. [5]. Although mixed hemorrhoids are not fatal or malignant, these symptoms can reduce a patient’s quality of life and have negative psychological and physical effects [6]. The treatment types include conservative treatment and surgical treatment. Mixed hemorrhoids with mild symptoms can be treated conservatively [7]. However, surgery is the initial treatment of choice in patients with symptomatic grade III–IV hemorrhoids [5, 6, 8]. Various surgical procedures have been used to treat symptomatic hemorrhoids in recent years, but (Milligan-Morgan) ligation is still considered the standard surgical procedure [9–13]. At the end of the operation, the wound is bandaged by a pressure dressing, which is the most traditional type of dressing that has been used clinically for many years [14]. The main purpose of pressure bandaging is to stop bleeding, but it may increase the incidence of postoperative complications, such as urinary retention, pain, anal swelling, and medical adhesive-related skin damage [12, 15–18]. Besides, clinical observation shows that with medical advances and the application of hemostatic drugs, the incidence of active bleeding within 24 h after modified Milligan-Morgan hemorrhoids surgery is very low. In addition, the necessity of pressure dressing after hemorrhoidectomy has received little scientific attention. A previous controlled trial included 67 patients who underwent Milligan-Morgan hemorrhoidectomy [19]. The data indicated that the use of a nonpressure dressing after hemorrhoidectomy reduces the incidence of urinary retention and catheterization. However, the incidence of severe postoperative bleeding and other postoperative complications was not assessed. There is no consensus on whether it is necessary and beneficial to use a nonpressure dressing after hemorrhoidectomy. The results of this randomized clinical study will preliminarily help answer this question.

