### Sample size {14}

The results of this study will be compared with the two-sided, two-sample chi-square test. The sample size should provide 80% statistical power at a significance level of 0.05, and a sample size ratio of 1:1. In the preliminary trial, the incidence of urinary retention was the main outcome measure and was 44.7% in the nonpressure dressing group and 24.7% in the pressure dressing group. Considering an anticipated dropout rate of 10%, we plan to include a total of 186 participants, with 93 participants per group.

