### Statistical analysis

The validity analysis of the study will be mainly based on intention-to-treat (ITT, all randomized cases) and per-protocol analyses (PP, cases that comply with the trial protocol, good compliance, and completed CRF). First, the Shapiro-Wilk test will be used to test whether the quantitative data follow a normal distribution. If the data are normally distributed, the mean value and standard deviation will be used to describe the quantitative data, and a *t* test will be used for analysis. Nonnormally distributed data will be expressed as the median and quaternary and compared using the Mann-Whitney *U* test. The qualitative data will be expressed as the frequency and percentage; non-grade data will be compared by the chi-square test, and grade data will be compared by the Mann-Whitney *U* test. Randomization will be performed 24 h prior to the surgical intervention. Data will not be collected and analyzed for patients not undergoing surgical intervention. If the scheduled surgery is not performed, the study participant will be excluded from the clinical trial. For every patient who is excluded from the trial after randomization and before the start of the observation period (postoperative wound with or without compression), another study participant will be included to achieve the number of cases needed. The randomization sequence will continue. The next patient will not necessarily be assigned to the same group as the excluded patient. This research will continue until the required number of evaluable patients is reached. Due to complications, a very small number of patients may not be able to comply with the randomly assigned treatment. The study will not exclude these patients. All statistical tests will be two-sided, and *P* < 0.05 will be considered statistically significant. If baseline factors are inconsistent between the two groups, subgroup analysis and multivariate analysis will be considered.

In the safety analysis, Fisher’s exact test will be used to compare the incidence of AEs and SAEs by category (severity) between the two groups.

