## Discussion

Pressure dressings are commonly used and have been considered a clinical standard for wounds after mixed hemorrhoid operations in China. However, these dressings can lead to some postoperative complications, and there are few reports on improvements in wound dressing methods after hemorrhoid surgery. This study will be carried out to determine whether nonpressure bandaging can be used routinely after open hemorrhoidectomy and whether it may be considered in specific circumstances.

During the operation, the patients will be treated with general anesthesia, and the method of applying a pressure dressing is complicated, so at least two medical staff will perform wound bandaging; nonpressure dressings need only a self-adhesive foam dressing, and only one medical staff member will be needed to perform wound dressing, and the process takes less time. The nonpressure dressing method can not only reduce the workload of medical staff but also save time.

Methods to minimize bias were implemented whenever possible. Randomization was performed 24 h before surgery. Randomization ensures a statistically consistent baseline between the experimental and control groups. However, one limitation of this study is that the researchers and patients cannot be blinded to the group assignments. The blinding of patients is an important way to prevent bias, but unfortunately, this step cannot be carried out in this study. However, the observers can be blinded. Before conducting any trial-related procedures, the researcher will obtain a written informed consent from each potential research participant. Randomization will be performed with a random number table generated in Excel, and then, the patients will be assigned a group according to the order of admission.

The research plan is consistent with clinical practice to the greatest extent possible to ensure complete and trouble-free data collection. Observation indicators such as pain and anal swelling may have affected the evaluation at certain time points while the patient is sleeping. Missing data are expected in these cases, but they should be minimized. The research leader will bear full legal responsibility for the entire study and publish the data on the website of the Clinical Research Management Department of West China Hospital of Sichuan University. Anyone who needs data can contact the author.

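### The trial asks whether nonpressure dressing is inferior on severe bleeding, but it is sized and tested only for two-sided differences, with no margin, so a non-significant bleeding result could not answer the question

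*Protocol article*

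**What the plan says.** **The question.** The Abstract (Methods) gives the purpose as determining "whether the use of nonpressure dressings after open hemorrhoidectomy is inferior to the use of pressure dressings in terms of severe postoperative bleeding", together with postoperative complications. It lists as one of two primary endpoints "the incidence of severe postoperative bleeding 1 h after dressing removal, which requires revision surgery within 24 h after the surgery". The Discussion says the study is carried out "to determine whether nonpressure bandaging can be used routinely after open hemorrhoidectomy".

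**The design.** Sample size {14} states: "The results of this study will be compared with the two-sided, two-sample chi-square test". It continues: "The sample size should provide 80% statistical power at a significance level of 0.05, and a sample size ratio of 1:1". The only rates entered are for urinary retention (44.7% and 24.7%). With 10% dropout this leads to 186 participants, 93 per group.

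**The analysis.** Statistical analysis assigns the t test, Mann-Whitney, chi-square or Fisher test by type of data and adds: "All statistical tests will be two-sided", with P<0.05 as the threshold. No margin or non-inferiority hypothesis appears.

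**The event rate.** Background and rationale {6a} gives no number for bleeding, only that "the incidence of active bleeding within 24 h after modified Milligan-Morgan hemorrhoids surgery is very low".

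**The standing of bleeding.** Objectives {7} lists urinary retention as the only primary objective and puts the hemostatic score among the secondary ones. Outcome measures {12} calls that score the other primary outcome, under the heading for secondary measures.

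**The concern.** The Background gives stopping bleeding as the main reason for a pressure dressing. A decision to leave it off routinely therefore needs evidence that re-operation for bleeding does not rise by an unacceptable amount. A two-sided difference test can show that two rates differ. When it is not significant, it does not show that they are close enough. That requires an interval set against a stated margin, and enough patients for the interval to be informative.

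Here the number of patients comes from a different and far more frequent endpoint. The risk is that the trial's central safety question ends with P>0.05 on a handful of events and no agreed rule for what that permits anyone to say.

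**Working it through.** **Step 1. Reproduce the plan's own figure.** Inputs from Sample size {14}: 0.447 and 0.247, two-sided alpha 0.05, power 80%, 10% dropout.

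n per arm = (1.96 + 0.842)² × [0.447×0.553 + 0.247×0.753] / (0.447 − 0.247)² = 7.849 × 0.4332 / 0.04 = 85.

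85 × 1.1 = 93.5, against the stated 93. (Dividing by 0.9 gives 94.4.) So 186 is a two-sided difference design on retention. Bleeding and a margin play no part in it. After 10% dropout, 93 × 0.9 ≈ 84 per arm are evaluable.

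**Step 2. Power to detect a rise in bleeding.** The document gives no bleeding rate, so the rates below are assumptions. Power is the sum of Bin(x; n, p₁) × Bin(y; n, p₀) over all outcomes (x, y) at which the test gives P<0.05, with uncorrected chi-square or Fisher.

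| Assumed rates (pressure vs nonpressure) | Chi-square, 93 per arm | Fisher, 93 per arm | Chi-square, 84 per arm | Fisher, 84 per arm |
|---|---|---|---|---|
| 1% vs 3% | 12.9% | 2.7% | 11.1% | 1.9% |
| 2% vs 4% | 10.8% | 3.7% | 10.1% | 2.9% |
| 2% vs 6% | 25.8% | 15.0% | 23.5% | 12.2% |
| 1% vs 5% | 34.7% | 16.4% | 31.3% | 12.8% |

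**Step 3. What a non-significant result leaves open.** The Newcombe 95% interval combines the Wilson limits of the two arms.

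- 0 vs 0 events of 93: the Wilson upper limit is 1.96² / (93 + 1.96²) = 3.84 / 96.84 = 3.97%. The interval for the difference is −3.97 to +3.97 points. With 84 per arm it is ±4.37 points.
- 3 (nonpressure) vs 0 of 93: chi-square P = 0.081, Fisher P = 0.246. The interval is −1.3 to +9.1 points, so a result that is not significant is still compatible with a 9-point excess.

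**Step 4. Could 186 patients support a non-inferiority conclusion?** Assume equal true rates p and one-sided 0.025. By the normal approximation, the smallest margin with 80% power at 84 per arm is √[7.849 × 2p(1−p) / 84]:

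- p = 1%: √(7.849 × 0.0198 / 84) = 4.3 points
- p = 2%: √(7.849 × 0.0392 / 84) = 6.1 points

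These are optimistic. At 84 per arm the Newcombe limit for 0 vs 0 is already 4.37 points, so a 4.3-point margin would be missed with no bleeds at all. Enumerating as in Step 2, but counting the outcomes whose Newcombe upper limit lies below the margin, gives power of about 27% (p = 1%, 4.3 points) and 52% (p = 2%, 6.1 points).

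For a 3-point margin, the approximate total needed is 2 × [7.849 × 2p(1−p) / 0.03²] / 0.9. With rounding up this is 386 at p = 1% and 760 at p = 2%, and for the same reason these totals are likely too low. The margins are illustrations only, since the document states none.

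**The case against.** The strongest reply is that this is simply a difference trial on urinary retention. The term non-inferiority is never used. The inferiority wording occurs once, in the Abstract, and also covers complications on which nonpressure dressing is expected to do better. The body's only primary objective is retention. Read literally, asking whether a dressing is inferior can be put to a difference test.

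Part of this stands. The non-inferiority objective is a reading of the text and not a label in it. But the Abstract makes severe bleeding a primary endpoint and the Discussion ties the trial to routine use, so bleeding cannot be set aside as incidental. On the literal reading the test has little power to find inferiority (Step 2). On the safety reading a null result does not answer the question (Step 3).

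A reader might go further and infer that P>0.05 will be taken as proof of safety, and that the pressure dressing will then be dropped. The document does not say so: it sets no rule for reading a non-significant bleeding result and no recommendation that follows from one.

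A reader might also infer that any several-fold rise would be missed. That depends on the assumed rates: at 93 per arm, 1% vs 8% gives 67% power by chi-square (52% by Fisher), and 1% vs 10% gives 82% (72%).

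Nor is it a fault of substance that bleeding might fall under chi-square, Mann-Whitney or Fisher. Fisher's exact test is already assigned to adverse events, and severe hemorrhage is listed as one. Choice of test at small counts and interval method can be left to an analysis plan. A margin cannot be left so easily, because it belongs with the sample size, and the sample size is fixed here on another basis.

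**Conclusion.** The point holds in this form: the stated question on severe bleeding and the stated design do not match. The trial is sized and tested for a difference in urinary retention. At that size it has roughly 2% to 35% power to detect the assumed rises in bleeding in Step 2. Even two arms free of bleeding would leave an excess of about 4 points unexcluded. P>0.05 on bleeding could therefore not show that nonpressure dressing is not worse, and the document does not guard against that misreading.

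The mismatch itself rests on the text alone. The power and margin figures rest on assumed bleeding rates of 1% to 2% under pressure dressing. The 0 vs 0 limit depends only on the number of patients and the interval method.

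**What to change.** 1. State that the powered comparison is the two-sided difference in urinary retention, and use the same wording in the Abstract, Objectives and Sample size sections.
2. For bleeding that requires revision surgery, report events per arm and the risk difference with a 95% Newcombe or exact interval.
3. Permit a conclusion of not inferior only if the upper limit lies below a margin that is clinically justified and fixed before unblinding, in both the ITT and the PP analysis.
4. If no acceptable margin is attainable with 186 patients, restate the bleeding objective as a descriptive safety estimate, and say that no safety conclusion will be drawn from P>0.05.

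Under item 4 this costs wording only: no change to sample size, randomization or data collection. A non-inferiority claim at a tight margin would need more patients, as Step 4 shows. The price of the wording route is a more modest conclusion on bleeding.

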
### Objectives {7}

#### Primary objectives

Incidence of retention of urine within 24 h after operation

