#### Secondary objectives

To assess the impact of pressure dressings versus nonpressure dressings surveillance on:
Pain score within 25 h after operation (6H\18H\25H);The change in hemostatic effect scores within 25 h after operation;The incidence of medically adhesive skin lesions;The anal edema score within 25 h after operation (6H\18H\25H);The anal dilatation score within 25 h after operation (6H\18H\25H);Dose of analgesics within 24 h after operation;Hospitalization costs; andLength of stay.

To assess safety, the incidence of adverse events (AEs) and severe adverse events (SAEs) between the two study groups will be compared to illustrate the potential risk to patients with nonpressure dressings after hemorrhoidectomy.

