### Ancillary and post-trial care {30}

All participants will return to usual care after dressing removal at postoperative 24 h. As part of our safety protocol, we will monitor patients’ surgical wound pain, micturition, skin damage, and active bleeding. Any participants with the above abnormal situations will be contacted by the site coordinator who will inform the doctor for timely treatment.

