### Outcome measures {12}

#### Primary outcome measures

There will be two primary outcomes. The incidence of urinary retention within 24 h will be one of these; typically, patients cannot urinate by themselves after using a hot compress or drug assistance and finally undergo retention catheterization.

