#### Secondary outcome measures

Postoperative pain will be measured at rest with routine care at 6, 18, and 25 h by using a visual analog scale (VAS) after the surgical procedure. The scale will range from 0 to 10 points, with higher scores indicating more severe pain [21]: 0 = no pain, 1~3 = slight pain that can be tolerated, 4~6 = pain that can be tolerated but affects sleep, and 7~10 = unbearable pain that affects not only appetite but also sleep.The change in hemostatic effect scores within 25 h will be the other primary outcome. The effect of hemostasis will be graded using a 3-point ordinal scale: 0 = the dressing was not soaked before removal, 1 = there was no bleeding after changing the dressing due to excessive blood oozing, and 2 = postoperative bleeding requiring surgical revision occurred.The change in mean rectal tenesmus sensation scores within 25 h will be graded using a 3-point ordinal scale: 0 = no abnormal sensation; 1 = mild anal discomfort, occasionally abnormal sensation; 2 = strong foreign-body sensation; and 3 = strong foreign body sensation that is not easily relieved after rest or treatment.The incidence of medical adhesive-related skin injuries will be measured. The skin condition will be assessed by a senior wound specialist nurse. If there is no skin damage, “no” will be recorded. When any of the following situations occur, “yes” will be recorded: (1) exfoliation, (2) tension blisters, (3) skin lacerations, (4) contact dermatitis, and (5) allergic dermatitis. In the statistical analysis, the incidence of medical adhesive-related skin damage will be calculated by a statistician.The change in the mean anal edema score when the dressing is removed 24 h after surgery will be graded using a 4-point ordinal scale: 0 = no anal edema, 1 = mild edema (< 1/4 anal area ), 2 = moderate edema (1/4 to 1/2 anal area ), and 3 = severe edema (> 1/2 anal area ).The total dose of analgesics before removing the dressing will be recorded.The length of hospitalization will be recorded in days.Hospitalization expenses will be recorded.

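### The bleeding endpoint has conflicting status, definition and time window across the protocol, and no rule says how a second primary would count; urinary retention is primary throughout

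*Protocol article*

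**What the plan says.** Five places in the protocol article describe the primary endpoints.

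- **Abstract, Methods.** Two primaries: urinary retention within 24 h, and "the incidence of severe postoperative bleeding 1 h after dressing removal, which requires revision surgery within 24 h after the surgery". The second is a yes/no event. The Abstract also gives the trial's purpose as finding out "whether the use of nonpressure dressings after open hemorrhoidectomy is inferior to the use of pressure dressings in terms of severe postoperative bleeding".
- **Objectives, Primary.** One entry: "Incidence of retention of urine within 24 h after operation". Bleeding is not there.
- **Objectives, Secondary.** "The change in hemostatic effect scores within 25 h after operation" is listed among the secondary objectives.
- **Outcome measures, Primary.** "There will be two primary outcomes. The incidence of urinary retention within 24 h will be one of these". The second is not described under this heading.
- **Outcome measures, Secondary.** "The change in hemostatic effect scores within 25 h will be the other primary outcome". The score has three grades, 0 to 2. Only grade 2 is bleeding that leads to a revision operation; grades 0 and 1 concern soaking of the dressing and oozing.

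On timing, Ancillary and post-trial care states: "All participants will return to usual care after dressing removal at postoperative 24 h".

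Statistical analysis assigns chi-square to ungraded categorical data and Mann-Whitney to graded data, and uses two-sided P < 0.05 for every test. Sample size uses retention rates only.

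**The concern.** Bleeding is the main hazard of leaving out pressure: the Introduction says that stopping bleeding is the chief purpose of a pressure dressing, and that the previous controlled trial did not assess severe bleeding. Yet this is the endpoint whose status changes from section to section. Depending on where one reads, it is not primary, it is secondary, it is a co-primary ordinal score, or it is a co-primary binary event. These are different variables with different tests and different windows.

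If this is still open when the data arrive, the trial team could choose the variable, the test and the status of bleeding with results in view. A published claim on bleeding could then not be traced to a single prespecified analysis. The word change in the score's definition adds to the ambiguity, because no baseline score is described for an outcome that starts with the dressing.

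**Working it through.** **1. Status and definition, side by side**

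| Section | Status of bleeding | Variable | Window | Test implied by Statistical analysis |
|---|---|---|---|---|
| Abstract, Methods | Primary | Binary, revision surgery | 1 h after removal, and within 24 h of surgery | Chi-square |
| Primary objectives | Absent | – | – | – |
| Secondary objectives | Secondary | Change in score | To 25 h | Mann-Whitney |
| Primary outcome measures | A second primary is announced, not described | – | – | – |
| Secondary outcome measures | The other primary | Change in 0–2 score | To 25 h | Mann-Whitney |

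Urinary retention is primary in each of the three places that name a primary endpoint or objective in its own right: the Abstract, the Primary objectives and the Primary outcome measures.

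**2. The window.** Scheduled removal is at 24 h, so one hour after removal is 24 + 1 = 25 h. The Abstract also requires revision within 24 h. For a dressing removed on schedule, both conditions cannot be met. A bleed found at the 25 h check is outside the Abstract's endpoint but inside the score's window.

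**3. What the sample size covers.** Inputs from Sample size: rates 44.7% and 24.7%, two-sided 0.05, 80% power, 10% dropout. With unpooled variance:

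n = (1.960 + 0.842)² × (0.447 × 0.553 + 0.247 × 0.753) / 0.20² = 7.849 × (0.2472 + 0.1860) / 0.04 = 85.0 per arm.

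85.0 × 1.1 = 93.5 per arm, and 170 / 0.9 = 189 in total. The planned 93 per arm (186) agrees within rounding. It is reproduced from retention alone; no bleeding rate or margin enters.

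**4. Error if two primaries are each tested at 0.05**

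- Success on either one, independent tests of full size: 1 − 0.95² = 0.0975.
- If the second test is an uncorrected chi-square on a rare binary event, its true size is below 5%. The protocol gives no revision rate, so common rates of 1%, 2% and 5% are assumed. Error is 1 − 0.95 × (1 − size):

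| Assumed rate | Size, 84 per arm | Error | Size, 93 per arm | Error |
|---|---|---|---|---|
| 1% | 0.9% | 5.8% | 1.1% | 6.1% |
| 2% | 3.3% | 8.2% | 3.7% | 8.5% |
| 5% | 4.2% | 9.0% | 4.3% | 9.0% |

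(84 is 93 × 0.9, rounded up.)

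- Success only if both are met: no inflation above 5%.

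**5. What each rule would cost in power.** Splitting alpha to 0.025 lowers retention power from 78% to 69% at 84 per arm, or from 82% to 74% at 93. Requiring both leaves alpha alone, but joint power cannot exceed the power for bleeding. At assumed revision rates of 1% versus 5%, chi-square power by the normal approximation is about 33% at 84 per arm and 36% at 93.

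**The case against.** Four points can be made for the protocol.

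*Retention is fixed.* A reader might infer that the trial has no fixed success criterion at all. The text does not support that: retention within 24 h is consistently primary and is what the trial is sized on. Only the second endpoint is unsettled. This stands and limits the finding.

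*The multiplicity rule may lie elsewhere.* The article says a statistical analysis plan was approved, and it is not shown. Allocation of alpha and the success rule often sit there. No sentence adopts an either-one rule, so 9.75% is conditional and is the upper figure for independent tests. This also stands. It does not help with the main problem, because an analysis plan cannot make contradictory statements in the protocol agree.

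*The window is not strictly impossible.* Grade 1 of the score allows for a dressing changed because of oozing. An early change could put removal, the following hour and a revision all before 24 h. The Abstract's window therefore fails for scheduled removal, not in every case.

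*Unsuitability of the score is not shown.* A reader might infer that soaking grades would hide a difference in revision surgery. That depends on rates the documents do not give. With revision at 1% versus 5% and 93 per arm, Mann-Whitney rejects in about 5% of simulated trials if soaking is 15% versus 10%, in 14% if it is 10% in both arms, and in 42% if it is 10% versus 15%. The direction is open, so the point does not rest on it.

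**Conclusion.** The contradiction is in the text and needs correcting. The bleeding endpoint has no single status, variable or window, and the choice changes the test and whether a bleed at 25 h counts. The 80% power applies to urinary retention only.

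The error consequence is conditional. It is up to 9.75% if success on either primary is claimed at 0.05 each, about 6% to 9% if the second test is chi-square at assumed revision rates of 1% to 5%, and no inflation if both must be met. The article does not say which rule applies. The finding does not extend to retention, whose definition as a primary endpoint is stable.

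**What to change.** 1. Make urinary retention within 24 h the single primary endpoint at two-sided 0.05. This agrees with the Primary objectives and the Sample size section.
2. Define severe bleeding once, as bleeding that leads to surgical revision at any time from the end of surgery through the 25 h check. Report it as the key secondary or safety endpoint, as a risk difference with a confidence interval. An interval also suits the Abstract's inferiority question better than a significance test, since no margin is given.
3. Keep the hemostatic score as an ordinary secondary outcome and drop the word change.
4. Align the Abstract, the Primary and Secondary objectives, and the Primary and Secondary outcome measures.

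If bleeding is kept as a second primary, the plan must state the decision rule with matching alpha, and say that the 80% power refers to retention only. Requiring both endpoints to succeed is not a free alternative, because a rare event would cap the joint power.

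Cost: a protocol amendment and a registry update, with no extra patients or data. The article reports recruitment as still under way. The price is that bleeding loses primary status.
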